### Personnel training

To validate and harmonize the methodologies, a general training meeting was held with all of the PIs and the ELANS coordination center. The scientists in charge of every research tool attended the meeting. At the end of this training, national teams were placed in charge of translating the field protocol into the local language and submitting the protocol to the local ethical review boards of the participating institutions. Each study site was also responsible for training their personnel for the pilot and field studies. The interviewers were required to have completed at secondary education. Training lasted from 7 to 10 days at each site.

### Quality control strategies

Quality control strategies were applied using a framework that comprehensively considered each phase of the study. To ensure accurate, standard and consistent measurements throughout this multicenter study, a variety of procedures were used and are described in Table 3. One the key aspects of the quality control was the development of the manual of operations to keep same methodology and procedures among all sites. The crucial roles of the PIs were focused on supervising of pilot test and fieldwork, identify and decide on the necessary amendments to the study protocol, coordinate all the trainings, ensuring accuracy of data entry and identifying inconsistencies and standardized procedures across the sites. The coordinating center audited the complete procedures for the countries.

**Table 3 Tab3:** Quality assurance strategies

Levels of quality control	Phases			
	Design and planning	Pilot testing	Data collection	Data analysis
Coordinating center	•Critical review of protocols •Harmonization of manual of operations for eight study sites •Coordination of timelines and activities	•Smoothness and feasibility of field operations assessed	•Monitoring field activities	•Audit and evaluate validity of findings prior to publication •Internal peer reviews prior to publication
Principal Investigators	•Review of design and planning of the study •Regular meetings with coordinating center	•Audit after completion of the pilot	•Supervising and ensuring accuracy of data entry	•Validity checks •Results review
Field Personnel	•Extensive training over a period of 7 to 10 days-theory and practical-by the study managers	•Evaluated all field and documenting difficulties	•Field coordinator will assure that procedures for data collections and quality control are followed •Additional training when necessary	
Survey Questionnaires	•Peer-reviewed •Validated •Translated to local languages	•Consistency in small pilot study will be established	•Regular checks done to assess completeness	•Incomplete questionnaires identified and discarded
Measuring Equipment	•Standardization of equipment and measurements •Acquired by each country •Development of anthropometric procedures manual	•Evaluation of calibration techniques, acceptability of use in field	•Regular calibration of equipment; faulty equipment replaced when required	
Documentation	•Assurance of standardized procedures across the sites •Training in appropriate and legible documentation	•Recording legibility assessed	•Audit recordings	
Data Storage & Confidentiality	•Data back-up and protection policies established	•Accessibility of software assessed	•Identify inconsistencies •Corrective actions •Locked and password protected data storage •Active back-up	•Datasets identified •Access to personal identifiers limited
Data Entry	•Training of staff •Protocols, consistent data cleaning methods and verification systems established	•Variability assessments conducted	•Interim analyses to identify duplicate entries	•Reporting of outliers •Validity checks •Database errors tracked

### Analysis plan

The primary outcome of interest will be to describe the distributions of overweight and obesity, and energy intake and expenditure intake across the countries and regions of the study. A secondary objective of the study will be to identify the individual characteristics associated with the two main outcomes of interest (obesity and energy intake/expenditure) and to test whether these associations vary across the different regions by applying the statistical methodologies described below. These individual characteristics of interest will include, but are not be limited to, education, marital status, age, sex and individual income. The results of the three main outcomes will also be presented after stratification for each of the individual characteristics.

Initially, basic statistical models will be applied to analyze the aggregated results for all the individuals in the multicenter study to identify the individual characteristics (independent of area of residence) associated with each of the outcomes, with the inclusion of all the projected 9000 individuals. Separate individual models for each of the countries will also be performed.

We will also test the presence of statistically significant differences between regions of residence and countries by adjusting multilevel models (also known as hierarquical linear models), where the individual results will be included as the first level of the model and the region of residence as the second level of the model. Overweight and obesity will be analyzed separately as dichotomous dependent variables (vs. normal weight) by adjusting logistic multilevel models, while energy intake and expenditure will be treated as continuous dependent variables and multilevel linear models will be adjusted. We will test for a statistical difference of the dependent variables according to region of residence (a two-level model) and also by including the country of residence as the third level of the previous multilevel models. Statistical difference between the regions and the countries will be tested by analyzing the area-level variance (between-group variation) of each multilevel model.

Another objective will be to identify the pathways that could lead to overweight/obesity and higher energy intake/expenditure. Some of the candidates include lower income leading to higher consumption of nutritionally poor products leading to obesity, marital status leading to higher energy intake, among many other possibilities. These options will be tested by adjusting Structural Equation Models (SEM), where each of the pathways that lead to the dependent variables will be tested independently for statistical significance. We will also calculate the Standardized Root Mean Square Residual (SRMR) for each of the final structural models to assess its goodness-of-fit, with the objective of selecting the models with the pathways that best fit the data. Finally, given the multicentric nature of the sample, we will also fit structural models with clustered standard errors to relax the assumption of independence of observations within clusters of regions and countries.

Further specific sub-projects will depend on the results and associations found for the initial analyses. Some of these sub-projects include analyses of micronutrient ingestion, snack consumption and the determinants of regular physical exercise levels. Other projects will follow depending on the results and associations observed in the main analyses. Some of the individual variables regarding dietary and physical activity patterns will likely be aggregated, depending on their interdependent relationships and previous studies in the literature, by applying factor analysis. The final datasets compiled from each country will be standardized into groups of variables and categories and sent to the coordinating center in Brazil. Descriptive statistical analyses, multilevel analyses, and structural equation models will be performed with R 3.2.0, MLwiN 2.29, and Stata 13, respectively.

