### Sampling procedures

A random complex, multistage sampling of 9000 adolescents and adults aged 15.0–65.0 years, stratified by geographical location (only urban areas), gender, age and socioeconomic status was performed to select a representative sample of the urban household population of eight Latin American countries. Only urban areas were included in order to keep homogeneous population in the research, and based on the fact that almost all countries have at least 80–90 % of their population living in urban areas. Individual quotas were defined for each of these variables, which allow the identification of the total numbers of interviews required to properly represent the socio-demographic distribution under study. The survey was designed in order that no more than one subject were selected from a household.

The sampling size was calculated with a confidence level of 95 % and a maximum error of 3.49 %. A survey design effect of 1.75 was estimated based on guidance from the U.S. National Center for Health Statistics [27], and calculations of the minimum sample sizes required per strata (i.e., socioeconomic level (SEL), age, and gender) were performed for each country. Table 2 shows a detailed description of the case numbers required per strata in each of the 8 study sites.

**Table 2 Tab2:** Estimated distributions of country-specific samples according to age range, gender, and SEL

	Age range				Gender		SEL			Total sample size	Margin of error (%)
	15–19.9 years	20–34.9 years	35–49.9 years	50–65 years	Male	Female	High	Middle	Low		
Argentina	144	444	336	276	576	624	72	504	624	1200	2.83
Brazil	220	760	600	400	940	1060	520	940	540	2000	2.19
Chile	113	305	270	183	426	444	61	348	461	870	3.32
Colombia	148	443	357	283	615	615	62	357	812	1230	2.79
Costa Rica	111	300	229	150	395	395	87	450	253	790	3.49
Ecuador	128	312	224	136	400	400	104	576	120	800	3.46
Peru	165	440	308	187	528	572	209	374	517	1100	2.95
Venezuela	143	418	319	220	528	572	55	154	891	1100	2.95

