The demographic data were obtained from the appropriate national statistics institutes of each country. The selection of the households was design in four stages. In the first stage, total urban population was employed to define main regions proportionally in each country first, and then select cities representing each region - main cities and other cities representatives of the region, mixing a random method and sampling criteria, and trying to fulfill urban population coverage to the maximum possible. This mixed criterion enabled an increase in the efficiency of the fieldwork according to the study characteristics. In the second stage, sampling points (census tracts) of each city were randomly selected. In the third stage, a cluster of households was selected from each sampling unit. Addresses were chosen systematically using standard random route procedures, beginning with an initial address selected at random and selection of households with three systematic jumps, that is, the selection of a given household was made by randomly picking the first home and subsequently skipping 3 households. Finally, in the fourth stage, selection of respondent within a household was performed using two criteria: in each sampling unit, half of the households the participant was selected by the next birthday criteria; in the other half selection was by quotas of gender, age, and SEL.

The field interviewer arrived at the home, show an official identification badge, a letter introducing ELANs study, and briefly explain the survey’s purpose. A screener questionnaire to enumerate the household and to determine eligibility to participate further in ELANS was fulfilled. Thereafter, the selected participant signed the informed consent form.

A telephone number was available for the participants in order to answer any questions about the research, and use of the accelerometer device.

In the following circumstances - unsuccessful attempts to contact the target individual, total refusal to participate, obstruction by a family member, or inability to participate for a specified reason (e.g., travel, agenda, hospitalization) - substitutes were chosen in the home next door, following the same random selection criteria described above.

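### The multilevel models stop at individual, region and country, so census-tract and city clustering enters the region variance being tested and can understate standard errors

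*Protocol article*

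**What the plan says.** **Design (Protocol article, Sampling procedures).** The sample is described as "A random complex, multistage sampling of 9000 adolescents and adults aged 15.0–65.0 years". Selection goes from regions to cities, then to tracts: "In the second stage, sampling points (census tracts) of each city were randomly selected". A cluster of households is then taken in each tract, and one respondent in each household. The sample-size paragraph also states: "A survey design effect of 1.75 was estimated based on guidance from the U.S. National Center for Health Statistics".

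**Analysis (Protocol article, Analysis plan).** There are three layers.

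- First-step models: "Initially, basic statistical models will be applied to analyze the aggregated results for all the individuals in the multicenter study", "with the inclusion of all the projected 9000 individuals". Separate models for each country are also planned. No variance method is given for either.
- Multilevel models, logistic for overweight and obesity and linear for energy intake and expenditure: "the individual results will be included as the first level of the model and the region of residence as the second level". Country is then added as a third level. Differences between regions and between countries are to be tested through the area-level variance.
- Structural equation models: "we will also fit structural models with clustered standard errors to relax the assumption of independence of observations within clusters of regions and countries".

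City and census tract appear in none of the listed models.

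**The concern.** People in the same tract tend to resemble each other in income, education, diet and weight. The plan accepts this when it assumes a design effect above 1. The multilevel models are where the plan deals with area, and their levels are named. Those levels leave out the two stages at which respondents were actually grouped within a region.

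Two things follow:

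- **Region test.** A region mean is an average over a limited number of tracts and cities. If the model has no term for these, their chance variation looks like variation between regions. The test of region variance can then report regional differences that are only neighbourhood clustering. Measuring variation by region is one of the stated aims in the Background.
- **Coefficients.** Standard errors for characteristics that cluster within tracts, such as education and income, tend to be too small. The same holds in the pooled and country-specific models if they are fitted without a clustering adjustment. This bears on the secondary objective, which asks which individual characteristics go with obesity and energy balance.

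**Working it through.** **Inputs from the article.** Confidence level 95 %, design effect D = 1.75, pooled n = 9000, Table 2 country sizes and margins. **Not given:** number of regions, tract cluster size, the share of D that comes from tracts, and how strongly covariates cluster. These are assumptions below, shown as ranges.

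**1. The plan's own figure.** The text says: "The sampling size was calculated with a confidence level of 95 % and a maximum error of 3.49" (per cent). For Costa Rica, n = 790 and p = 0.5:

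1.96 × √(0.25/790) = 3.49 %

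All eight margins in Table 2 reproduce in this way to rounding, as simple-random-sampling margins. With D = 1.75 the Costa Rica margin would be 3.49 × √1.75 = 4.61 %. So the design effect is stated but does not show in the printed precision. Here it serves only as the plan's own statement of how strong the clustering might be.

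**2. Region-variance test.** Assume a balanced linear model, no true region difference, and tracts nested in k regions. The between-region mean square is inflated by the tract design effect D, and the within-region mean square is almost unchanged at n = 9000. The F statistic then behaves as D × F(k−1, n−k), and

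rejection rate = P( F(k−1, n−k) > F₀.₉₅ / D )

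| Regions k (assumed) | F₀.₉₅ | Rejection, D = 1.75 | Rejection, D = 1.2 |
|---|---|---|---|
| 8 | 2.011 | P(F > 1.149) = 33 % | P(F > 1.676) = 11 % |
| 24 | 1.530 | P(F > 0.875) = 63 % | P(F > 1.275) = 17 % |
| 40 | 1.401 | P(F > 0.800) = 81 % | P(F > 1.167) = 22 % |

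A simulation with tracts of 10 households agreed with the D = 1.75 column to within about one percentage point. The F test stands in for the planned test of a variance component; the logistic models were not computed.

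**3. Upper bound for coefficients.** If D = 1.75 applies in full and is ignored:

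- correct standard error / independence standard error = √1.75 = 1.32, so the latter is 1 − 1/1.32 = 24 % too small
- type I error = 2 × (1 − Φ(1.96/√1.75)) = 13.8 %
- coverage of a 95 % interval = 86.2 %

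This is the case of a covariate that is constant within a tract.

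**4. Covariates that vary within a tract.** Use D_x = 1 + (m−1) ρ_y ρ_x, where m is the cluster size and ρ_y and ρ_x are the within-tract correlations of outcome and covariate. Setting 1 + (m−1) ρ_y = 1.75 gives (m−1) ρ_y = 0.75, so m cancels and D_x = 1 + 0.75 ρ_x.

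| ρ_x (assumed) | D_x | Standard-error factor | Type I error |
|---|---|---|---|
| 0 | 1.000 | 1.00 | 5.0 % |
| 0.1 | 1.075 | 1.04 | 5.9 % |
| 0.3 | 1.225 | 1.11 | 7.7 % |
| 0.5 | 1.375 | 1.17 | 9.5 % |
| 1 | 1.750 | 1.32 | 13.8 % |

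**The case against.** Much can be said for the plan.

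- **It is a condensed article.** The variance method and covariate list of a preliminary model are commonly left to the full plan. This stands for the first-step and country-specific models: the text is silent on clustering there, and silence alone is no error. It does not cover the multilevel models, whose levels the article states.
- **Country.** A reader might infer that the pooled models have no country term and so mix within-country with between-country associations. The documents do not establish this. The parenthesis about area of residence can mean that area is ignored or that it is adjusted for. Separate country models are also planned, and these cannot mix the two.
- **Structural equation models.** A reader might include these in the criticism. Standard errors clustered on region or country already allow for any correlation among the tracts and cities nested inside. Having few clusters would be a different matter. It would turn on which unit is used, and the number of regions is not given.
- **Size.** A reader might take standard errors to be too small by the design effect itself. They scale with its square root, 1.32. The 1.75 was also set for the sample-size calculation, not for regression coefficients, and models with region and country effects already take up part of the clustering. So 13.8 % is a ceiling.
- **Primary outcome.** It is descriptive. This limits the coefficient problem to the secondary analyses. It does not remove the region problem, because regional comparison is part of what is to be described and tested.

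**Conclusion.** The concern holds in a limited form. The stated multilevel structure omits the tract and city stages of the sampling design, so following it as written puts their variance into the region variance under test.

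The false-positive rate of that test could be about 33 % (8 regions) to 63 % (24 regions) if all of the 1.75 came from tracts. It would be 11 % to 17 % if tracts contributed a design effect of 1.2. These figures rest on an assumed number of regions, an assumed tract share and a balanced linear model with n = 9000. The direction does not depend on those choices as long as some tract or city clustering exists.

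For coefficients the understatement is at most 1.32-fold, taking 1.75 at face value. Type I error is at most 13.8 %, and about 5.0 to 9.5 % for assumed within-tract covariate correlations of 0 to 0.5. A covariate that hardly clusters, as one would expect of sex, loses almost nothing. For the pooled and country-specific models, the point is only that no clustering adjustment is stated and one is needed.

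**What to change.** - In the multilevel models, add sampling point (census tract) and city as levels below region, and test region and country variance with those levels present.
- In the first-step pooled models and the country-specific models, state that standard errors are clustered on the selected sampling units, or that survey-design variance is used.
- Country fixed effects in every pooled model are not part of this change, since they would displace the country-level variance that the plan means to test.

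The cost is a little more analysis work and wider intervals. The tract and city identifiers must be carried into the analysis dataset. Both were selected units, so they should be on record, but the article does not say that they are kept, and this should be confirmed. The Background says fieldwork is only now ending, so the wording can still be settled before analysis.

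### The pooled models for individual characteristics name no area term, and no model carries the sampling point, so results can be wrong for characteristics that differ by country or cluster by area

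*Protocol article*

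**What the plan says.** The Analysis plan of the protocol article gives the secondary objective as finding which individual characteristics go with obesity and with energy intake or expenditure, and whether those associations differ by region. Education, marital status, age, sex and individual income are listed as examples. The steps are:

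- **Pooled models.** "basic statistical models will be applied to analyze the aggregated results for all the individuals in the multicenter study", in order to "identify the individual characteristics (independent of area of residence) associated with each of the outcomes", "with the inclusion of all the projected 9000 individuals". No country, region or sampling-point term is named.
- **Country models.** "Separate individual models for each of the countries will also be performed".
- **Multilevel models.** These are introduced for testing differences between regions and countries, "where the individual results will be included as the first level of the model and the region of residence as the second level", and "also by including the country of residence as the third level of the previous multilevel models". The test described is on the area-level variance.
- **Structural equation models.** Clustered standard errors are planned here only, with regions and countries as the clusters.

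Sampling procedures describes census tracts drawn at random within cities, with a cluster of households taken from each. It also states: "A survey design effect of 1.75 was estimated". Table 2 gives the planned sample by country, age, gender and socioeconomic level (SEL).

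**The concern.** A pooled regression without area terms mixes two associations: the one between people within a country and the one between countries. If a characteristic is distributed differently across countries, its coefficient takes up part of any country difference in the outcome, whatever its cause. It can then appear associated with obesity when it is not associated within any country, or a real association can be diluted or reversed.

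The second issue is precision. People in the same tract resemble each other in outcome and often in socioeconomic characteristics. A model that treats them as independent gives standard errors that are too small for characteristics that cluster by tract. A region or country random effect does not remove the correlation within tracts.

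The pooled results also matter beyond the first step, because the Analysis plan makes later sub-projects depend on the associations found in the initial analyses.

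**Working it through.** **1. The plan's own precision figure.** With p = 0.5, margin = 1.96 × √(0.25/n). For Costa Rica, 1.96 × √(0.25/790) = 3.49 %, as printed in Table 2. The other seven margins reproduce in the same way. With the stated design effect, Costa Rica would be 1.96 × √(1.75 × 0.25/790) = 4.61 %. The printed margins therefore also leave clustering out.

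**2. Which characteristics are exposed to country differences (Table 2 only).** Share of variance explained by country = [Σ n(p − p̄)²/N] / [p̄(1 − p̄)], with N = 9,090, the sum of the Table 2 totals.

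- Low SEL: from 120/800 = 15 % (Ecuador) to 891/1,100 = 81 % (Venezuela); p̄ = 4,218/9,090 = 0.464. Ratio 0.0393/0.2487 = about 16 %.
- Male sex: 47 to 50 % in every country; p̄ = 4,408/9,090 = 0.485. Ratio 0.00013/0.2498 = about 0.05 %.
- Age, using band midpoints: about 0.4 %.

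Income and education are not tabulated. That they behave like SEL is an inference.

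**3. Tract clustering alone.** Assume 10 people per tract (not in the document). A design effect of 1.75 for the outcome then implies a tract correlation of 0.75/9 = 0.083. For a coefficient, design effect d = 1 + 9 × ρx × 0.083, where ρx is the tract correlation of the characteristic (assumed). Actual level of a nominal 5 % test = 2 × [1 − Φ(1.96/√d)].

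| ρx | d | actual level |
|---|---|---|
| 0.02 | 1.015 | 5.2 % |
| 0.05 | 1.04 | 5.4 % |
| 0.3 | 1.225 | 7.7 % |
| 0.5 | 1.375 | 9.5 % |
| 1 (full 1.75) | 1.75 | 13.8 % |

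The first two rows are plausible for sex or age. The last row is the ceiling: the standard error would need multiplying by √1.75 = 1.32, and 9,000 people would carry the information of 9,000/1.75 = 5,143. The country-specific models face the same levels.

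**4. Tract clustering plus country differences.** Simulated pooled regression with Table 2 country sizes, tracts of 10, outcome tract correlation 0.083, ρx = 0.3, no true association and 1,500 runs per case. The country shares are assumptions.

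| country share of outcome / characteristic | pooled, no area term | independent repeats |
|---|---|---|
| 0 / 0 | 8 % | 7 % |
| 1 % / 5 % | 15 % | 13 to 14 % |
| 2 % / 5 % | 20 % | 19 to 20 % |
| 3 % / 10 % | 35 % | 33 to 34 % |

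With country indicators and errors clustered on the tract, rejection was about 4 to 6 % throughout.

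**5. A second route, using the Table 2 low-SEL shares.** Assume mean obesity prevalence of 25 %, no SEL effect within any country, and a correlation of 0.5 between country prevalence and low-SEL share. With a between-country SD of 2, 3 or 5 percentage points, the crude pooled odds ratio for low SEL is about 1.04, 1.06 or 1.11, and false rejection is 14, 26 or 57 %. At correlation 0 the odds ratio is about 1.00 and rejection is 5.6, 6.4 or 8.9 %.

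**The case against.** A reader might infer that the plan leaves country and region out altogether, so that country differences will pass as individual associations. The document does not support that.

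- The article lists no covariates for the pooled models. Its aim, "to identify the individual characteristics (independent of area of residence) associated with each of the outcomes", can mean that area is ignored or that associations are net of area. The omission is the natural reading but not the only one, and a full analysis plan might settle it.
- The pooled step is only the first. The country-specific models are free of between-country confounding. The region and country models also serve the secondary objective, because that objective is tied to all the methods that follow and asks whether associations vary by region.
- The inflation is not general. Sex and age, two of the five named characteristics, are hardly touched.
- The sizes rest on correlations and a tract size that the document does not give, and 1.75 is a planning value.

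All of this stands and limits the point. What remains is that the article does not say which model conclusions on individual characteristics come from, and that every level or cluster it names is region or country. Clustering on region would cover the tracts inside it, but it is planned only for the structural models. The basic, country-specific and multilevel regressions, as described, have no allowance for tracts.

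**Conclusion.** The point holds in a limited form. As described, the pooled step names no area term and no model carries the sampling point, although the protocol assumes a design effect of 1.75. For SEL, and probably income and education, pooled associations can mix in country differences and standard errors can be too small.

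The actual level of a nominal 5 % test is about 7 to 8 % from tract clustering alone at a tract correlation of 0.3 for the characteristic, 9.5 % at 0.5, and at most 13.8 % if 1.75 applied in full. It is about 15 to 35 % if country also explains 1 to 3 % of the outcome and 5 to 10 % of the characteristic. Table 2 shows about 16 % for low SEL, so the assumption for the characteristic is not extreme; the share for the outcome is unknown.

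The evidence does not show that country confounding goes unaddressed in the plan as a whole, or that all standard errors are too small.

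**What to change.** - State that conclusions on individual characteristics come from models that include area: either country indicators with region as a random effect, or region indicators alone. Regions are defined within countries, so region indicators already absorb country, and fixed terms for both would be redundant.
- In the pooled, country-specific and multilevel models, cluster standard errors on the sampling point or include it as a level.
- Replace the phrase on independence from area with a plain statement of how area enters.
- If a pooled model without area terms is still shown, label it descriptive and do not test from it.

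The cost is wording, a few extra model terms and slightly wider intervals. No new data are needed, provided that the tract identifier is kept in the analysis file.

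### The multilevel models have no level for the census tracts through which people were sampled, so the test for regional differences does not hold its nominal error rate

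*Protocol article*

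**What the plan says.** The Analysis plan section fixes both the hierarchy and the test. In the first model "the individual results will be included as the first level of the model and the region of residence as the second level". A further model is formed by "including the country of residence as the third level of the previous multilevel models". The decision rule is that "Statistical difference between the regions and the countries will be tested by analyzing the area-level variance (between-group variation) of each multilevel model". Logistic models are planned for overweight and obesity, and linear models for energy intake and expenditure.

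The Sampling procedures section describes more stages than these models contain. Regions are defined within each country, and the next step is to "then select cities representing each region". After that, "In the second stage, sampling points (census tracts) of each city were randomly selected", and "In the third stage, a cluster of households was selected from each sampling unit". Because "no more than one subject were selected from a household", there is no clustering within households. The same section assumes a survey design effect of 1.75.

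No part of the article gives these multilevel models a tract or city level, or a design-based correction. The clustered standard errors at the end of the Analysis plan apply to the structural equation models, and only for regions and countries.

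**The concern.** People from one census tract are likely to resemble each other in diet, activity and weight. A model with nothing between person and region treats them as independent once region is accounted for. Regional means then vary more than the model expects even when regions do not differ, and the model can only attribute that excess to region. Adding country above region leaves the dependence below region untouched.

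What is at stake is which regional differences are declared real. Measuring variation by region is one of the three study aims in the Background, and the Discussion expects the findings to inform health policy and programmes.

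**Working it through.** **Inputs from the article.** Levels: individual, region, country. Sampling: region, city, tract, household cluster. Projected total: 9,000. Design effect: 1.75.

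**Inputs the article does not give, so assumed.** Number of regions K: 16, 32 or 40. Interviews per tract m: 5, 10 or 20. Significance level: 5 %. Clustering part D of the design effect: 1.75 (all of it) or 1.375 (half of the excess).

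**The article's own figure.** Table 2's largest margin of error, for Costa Rica, is 1.96 × √(0.25/790) = 3.49 %, as stated. It is reached without the design effect; with it, the margin would be 3.49 × √1.75, or about 4.61 %. So the table does not show how much of the 1.75 is clustering.

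**Step 1: approximation.** Set the true region variance to zero and choose the tract intraclass correlation ρ so that 1 + (m − 1)ρ = D. For m = 10 and D = 1.75, ρ = 0.75/9 = 0.083. The between-region mean square then has expectation of about D times the residual variance, so

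P(reject) ≈ P(χ² with K − 1 df > its 95 % point / D).

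For K = 40 and D = 1.75, the 95 % point is 54.57; 54.57/1.75 = 31.18; and P(χ² with 39 df > 31.18) = 0.81. For region within country the degrees of freedom are K − 8, which gives 35 % to 75 % at 1.75 and 19 % to 39 % at 1.375 for 16 to 40 regions.

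**Step 2: simulation by type of test.** The article does not name the test, so three were compared in the two-level model (continuous outcome, balanced regions, m = 10, 3,000 runs). Rejection in %, for 16 / 32 / 40 regions:

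| Test | D = 1.75 | D = 1.375 |
|---|---|---|
| F | 50 / 74 / 81 | 25 / 38 / 44 |
| Likelihood ratio, ML | 40 / 68 / 76 | 16 / 32 / 38 |
| Likelihood ratio, REML | 45 / 70 / 81 | 22 / 36 / 42 |
| Wald, two-sided | 1 / 27 / 39 | 0 / 4 / 9 |

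Separate runs differed by up to about four percentage points. Results hardly changed with m = 5 or 20. As a check, with no clustering and 40 regions the tests rejected in about 4–5 % (F), 3–4 % (likelihood ratio, ML) and 0.1 % (Wald).

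**Step 3: size of the spurious variance.** Its expected share of total variance is roughly (D − 1)/n, where n is the number of people per region. At D = 1.75 this is 0.75/562.5 = 0.13 % for 16 regions and 0.75/225 = 0.33 % for 40. Simulation gave 0.13 % to 0.35 % at 1.75 and slightly under 0.1 % to 0.18 % at 1.375.

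**Step 4: tract variation in the comparison.** With region tested against the tract mean square, rejection was 4.2 % to 5.7 % across the simulated settings.

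**The case against.** The strongest reply is that the size is not established. The 1.75 is a planning allowance taken from outside guidance, not an estimate of tract clustering for body mass index or energy intake, and some of it may be weighting. The test is unnamed, and a Wald test is conservative with few regions. With 5 regions and 1,100 people at D = 1.75, the F test rejects in about 25 %, the likelihood ratio in about 14 % and Wald in about 0 %. All of this stands, and it is why the result is given as a range.

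Four stronger readings are tempting, and the document supports none of them:

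- A reader might infer that all tract variation is counted as region variance. Most of it stays in the individual residual; only what fails to average out over a region's tracts reaches the region level.
- A reader might infer that the primary result is compromised. The stated primary outcome is descriptive and does not depend on these levels; the variance test is an additional analysis.
- A reader might take the rates near 80 % as the error rate of the plan. They need about 40 regions, all of the 1.75 as clustering, and an F or likelihood-ratio test.
- A reader might add that standard errors for characteristics that cluster by neighbourhood are too small. That is plausible, but nothing here puts a figure on it.

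Nor can the gap be put down to the brevity of an article. The article lists the levels and the test itself, so this is a stated choice.

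**Conclusion.** The point holds. The levels named in the Analysis plan do not match the sampling described in Sampling procedures, and as written the test of region variance does not have its nominal level. Under the assumptions above, the inflation is large for the F and likelihood-ratio tests, even if only half of the excess design effect is clustering. For a Wald test the direction depends on the number of regions: about 0–1 % rejection with 16 and about 40 % with 40 at a clustering design effect of 1.75.

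The damage is mainly to the test and much less to the estimated amount of regional variation. City clustering was not simulated; it would be expected to add to the inflation. The logistic models were not simulated either, but the same mechanism applies to them.

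**What to change.** Add the sampling point (census tract) as a level below region in both the linear and the logistic multilevel models. Add city as a level where a region has more than one sampled city; where it has only one, city and region variance cannot be separated, and the plan should say so. Name the test, and test the region variance by comparing two models that both keep these lower levels. Carry the sampling-point and city codes from fieldwork into the analysis file.

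The cost is a change of wording, two identifiers in the dataset, longer model runs, and a loss of apparent power for the region test. The sampling points were selected units, so their codes should exist. The article describes fieldwork as just ending and the analyses as still to come, so the change could be made before the models are fitted.
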